## Background

Unhealthy nutrition and lifestyle, characterized by a high caloric intake and vitamin deficiencies, derange metabolic and endocrine pathways and are causing obesity which contributes to the development of non-communicable diseases (NCDs), such as cardiovascular and metabolic diseases [1, 2]. Although awareness of the impact of unhealthy nutrition and lifestyle is increasing, its prevalence remains very high, not only in general, but also in the reproductive population in which health consequences range from subfertility to congenital malformations or even perinatal death [3–7]. Most evidence is available on the detrimental impact of maternal smoking, alcohol consumption and inadequate folic acid supplement use, which are strongly associated with embryonic growth and small for gestational age (SGA) and congenital malformations [8–12]. Currently, several studies that focused on the adherence of maternal dietary patterns have shown the benefits of healthy foods such as fruits and vegetables on perinatal outcome [13, 14].

In the Netherlands, particularly in large cities such as Rotterdam, perinatal mortality rates and the prevalence of perinatal complications, such as SGA, premature birth and congenital malformations (also referred to as Big3 complications), is relatively high compared to other European countries [15–17]. In order to reduce these prevalence rates, preconception care (PCC) should be implemented, focused on the promotion of health and the identification of (modifiable) risk factors of prospective parents as well as the next generation [18–20].

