In order to create awareness and to implement PCC on a large scale, new approaches need to be explored and (mobile) technologies can be used. Previously, we developed and implemented a preconception outpatient clinic tailored to improve nutrition and lifestyle of which the results were promising, i.e. 30% reduction of inadequate nutrition and lifestyle and a 65% increased chance of ongoing pregnancy after IVF treatment [4, 21]. However, this outpatient clinic could only provide PCC on a small scale due to the required expertise, time and costs. To overcome these barriers we have developed the personal mHealth coaching program ‘Smarter Pregnancy’ (Dutch version available on: www.slimmerzwanger.nl, English equivalent available on: https://www.smarterpregnancy.co.uk/research/), providing individual, tailored and continuous information on a large scale during 26 weeks. Previous studies have shown that women seek online information with regard to healthy nutrition and lifestyle which suggests that online interventions using mobile technology can be effective [22, 23]. Also, women embrace online anonymity to control and self-manage online information [24, 25]. Smarter Pregnancy identifies the most important risk factors regarding nutrition and lifestyle and subsequently provides tailored information and motivational coaching by text and e-mail messages [6].

We hypothesize that our mHealth program will effectively improve nutrition and lifestyle in couples contemplating pregnancy. Based on our previous studies and that of others we designed a randomized controlled trial (RCT) to study the effectiveness of “Smarter Pregnancy”, defined as a significant improvement of vegetable and fruit intake and folic acid supplement use, when started preconceptional [4, 6, 7, 21, 26]. This intervention can be considered as a primary prevention tool resulting in a reduction of Big-3 complications, perinatal morbidity and mortality in the short-term and NCDs in the long-term [2, 27, 28].

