### Objectives

A randomized controlled trial is conducted in two independent populations, i.e. couples from the general population and couples undergoing IVF/ICSI treatment, to study whether unhealthy nutrition and lifestyle can be improved by the Smarter pregnancy coaching program as an intervention tool. Furthermore, we will determine whether couples will have a higher pregnancy rate and if their risk for Big3 complications can be reduced by improving nutrition and lifestyle.

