#### Secondary outcomes

1) A reduction in smoking by women and men contemplating pregnancy; 2) pregnancy rates in couples; 3) birth prevalence rate of Big-3 complications in the entire study population; 4) cost-effectiveness of the Smarter Pregnancy intervention.

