### Recruitment, cohort composition and randomization

Women are invited to participate by a (health care) professional from their midwifery practice, children’s daycare, childhealth center, or hospital. Self-registration through the website is also possible. Potentially eligible participants are contacted after registration by one of the researchers to verify their eligibility, to provide more details and answer questions about “Smarter Pregnancy” and to confirm their registration.

Participants are allocated either in a general population cohort or the IVF/ICSI- (ART) population cohort, depending on whether they will receive fertility treatment. Randomization of the participants is stratified by cohort and per center of inclusion. For each stratum a permuted block design is used and programmed beforehand. Hereby, allocation concealment is ensured.

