### Statistical analysis

A flowchart will be used to depict the total participants of each cohort and divided per group, subdivided per gender. Also, the amount of resigning participants will be shown per time point (6 weeks). General and baseline characteristics will be compared between groups and shown in a baseline table.

The primary analysis will be based on intention to treat (ITT). For men and women in both the intervention and the control group the DRS will be calculated at baseline and after 24 weeks and used for further analyses. This continuous outcome measure will be analyzed by the ‘difference in difference principle’ and used in a linear regression model, including the initial/baseline value of the DRS. Repeated measurements will be used to investigate the effects of the intervention over time and the interaction of the intervention with socio economic status, ethnicity and age. Chi-square analysis and ANCOVA will be used to study the effects of the intervention on the pregnancy outcome and Big-3 complications.

To measure the compliance and reliability of ‘Smarter pregnancy’ we will analyze the percentage of randomized women who fill in the questionnaire after 12 weeks of participation and the percentage of participants who experienced technical problems. Corresponding confidence intervals will be given.

The influence on the primary outcome of participation of men, if pregnancy occurred during participation, age and low socio economic status will be analyzed by including these variables and their interaction with both groups, one by one in the model which will be used for the primary outcome. If there is heterogeneity of the treatment effect, the effect will be determined per subgroup separately.

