Currently, research in the field of mobile technology is mainly aimed on the use of mHealth in low- and middle-income countries, because this new form of health care delivery can reach the poorest regions in which the prevalence of NCDs and poor maternal and child health are the highest [35–38]. By our opinion, also high income countries comprise specific target groups, such as the reproductive population, in which risks for poor reproductive and pregnancy outcome accumulate, because of the lack of knowledge and self-efficacy with regard to PCC [39]. Therefore, we consider mHealth a promising method to approach the large group of reproductive women and men which is currently wrongly assumed to be at low risk for poor reproductive and pregnancy outcome, although it is known that the prevalence of risk factors in this population is high [4, 6, 11]. Given that 98.6% of all Dutch women and men between 18 and 45 years old have access to the internet and 96.2% can access the internet by their mobile phone makes this mHealth approach justifiable [40].

Strengths of this RCT are the longitudinal observations and the longitudinal biomarker validation in blood. Also, additional study questionnaires for short-term and long-term follow-up (respectively 12 and 26 weeks after the last questionnaire at 24 weeks), including sociodemographic data and medical record validation, are considered important strengths of this study. A limitation of this RCT is the potential selection bias, which is unfortunately inherent to participation in a study, especially on behavioral change, as well as the exclusion of participants without sufficient knowledge of the Dutch language.

With this RCT we expect to demonstrate the effectiveness of our Smarter Pregnancy program and its positive effect on reproductive and pregnancy outcome in both fertile and subfertile couples. Healthcare professionals are often also not aware of the importance of PCC nor have tools containing information and guidelines to provide nutrition and lifestyle care for medical practice [41]. Therefore, we consider this study a unique intervention regarding the implementation of accessible preconception care.

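### Big-3 complications are worded as a rate among births, a group the intervention is expected to change, and the tests named take no account of cohort or centre

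*Protocol article*

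**What the plan says.** All references are to the protocol article.

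- **Secondary outcomes**: pregnancy rate in couples is outcome 2. Outcome 3 is the "birth prevalence rate of Big-3 complications in the entire study population". The Background defines Big-3 as small for gestational age, premature birth and congenital malformations.
- **Statistical analysis**: "Chi-square analysis and ANCOVA will be used to study the effects of the intervention on the pregnancy outcome and Big-3 complications". The sentence names no stratification, no covariates and no matching of method to outcome. Intention to treat is stated for the primary analysis only.
- **Objectives**: "we will determine whether couples will have a higher pregnancy rate and if their risk for Big3 complications can be reduced". Raising pregnancy and lowering Big-3 risk are thus joint aims.
- **Background**: the group's earlier outpatient clinic is credited with "a 65% increased chance of ongoing pregnancy after IVF treatment". The **Discussion** expects the present programme to show "its positive effect on reproductive and pregnancy outcome in both fertile and subfertile couples".
- **Objectives**, on the populations: "A randomized controlled trial is conducted in two independent populations, i.e. couples from the general population and couples undergoing IVF/ICSI treatment". **Recruitment, cohort composition and randomization**: "Randomization of the participants is stratified by cohort and per center of inclusion".
- **Additional study questionnaires and follow-up**: the last questionnaire, which collects pregnancy outcome, comes one year after enrolment.

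**The concern.** A birth prevalence is ordinarily counted per birth, so only women who gave birth contribute. Whether a woman gives birth is settled after randomisation, and the trial's own hypothesis is that the intervention changes it. If it does, the intervention-arm births include some with no counterpart in the control arm. If those additional births carry a different Big-3 risk from the rest, the rate among births differs between arms even though the programme changed nothing in any given pregnancy. A real benefit could be masked, or an apparent one produced.

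A second route to the same problem opens if the cohorts are pooled. A larger rise in births in the IVF/ICSI cohort changes the cohort mix among births, and a crude chi-square attributes the resulting shift to the intervention.

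Third, the outcomes named are yes/no, while ANCOVA is a model for continuous outcomes. The text does not say what it is to be applied to.

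This is a secondary outcome, but it carries the public-health argument of the article, namely fewer perinatal complications.

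**Working it through.** **The plan's own figure.** None is given for pregnancy or Big-3. The sample-size figure for women concerns the dietary risk score: 2 × (1.960 + 0.842)² × 2.7² / 0.5² ≈ 458 per arm, 916 in total, as stated. It is not in question.

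**Inputs.** From the documents: the 65% figure (Background), the two cohorts and the randomisation strata. Every birth probability and Big-3 risk below is an assumption. All illustrations of the rate among births assume no effect on Big-3 in any given pregnancy.

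**A. Additional births at a different risk.** Assume 50% of controls give birth, with 10% Big-3. The intervention adds births in a further 10% of women.

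| Risk in added births | Big-3 among births, intervention | Control | Difference |
|---|---|---|---|
| 5% | (0.50×0.10 + 0.10×0.05)/0.60 = 9.2% | 10% | −0.8 points |
| 10% | (0.05 + 0.01)/0.60 = 10.0% | 10% | 0 |
| 20% | (0.05 + 0.02)/0.60 = 11.7% | 10% | +1.7 points |

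Per randomised woman, in the 20% row: birth without Big-3 is 0.45 in controls and 0.45 + 0.10×0.80 = 0.53 with the intervention; birth with Big-3 is 0.05 and 0.07.

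**B. Two risk groups of equal size.** Low-risk women: Big-3 risk 10%, birth probability 0.50 in both arms. High-risk women: Big-3 risk 25%, birth probability 0.25 in control and 0.35 with the intervention.
- Control: (0.50×0.10 + 0.25×0.25)/0.75 = 15.0%
- Intervention: (0.50×0.10 + 0.35×0.25)/0.85 = 16.2%
- Difference: +1.2 points. With equal birth probabilities in the two arms it is zero.

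**C. The 65% taken at face value, IVF/ICSI cohort.** This assumes that the figure carries over from another programme and from ongoing pregnancy to birth, so it is an outer case. Additional births are 0.65/1.65 = 39% of intervention-arm births. With 10% risk in the rest:
- added risk 5%: (0.10 + 0.65×0.05)/1.65 = 8.0%
- added risk 15%: (0.10 + 0.65×0.15)/1.65 = 12.0%
- added risk 20%: (0.10 + 0.65×0.20)/1.65 = 13.9%

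**D. Cohort mix under pooling.** General cohort: birth probability 0.60, risk 15%. IVF/ICSI: 0.25 and 25%. The risk within each cohort is the same in both arms.
- Control: (0.60×0.15 + 0.25×0.25)/0.85 = 17.9%
- IVF/ICSI births up 65%: (0.09 + 0.4125×0.25)/1.0125 = 19.1%, or +1.1 points
- IVF/ICSI births up 20%: (0.09 + 0.30×0.25)/0.90 = 18.3%, or +0.4 points
- Equal cohort risks: 0

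**E. Precision lost without stratification (pregnancy).** Assume 60% and 35% by cohort, with equal cohort sizes. Pooled variance: 0.475×0.525 = 0.2494. Mean within-cohort variance: (0.24 + 0.2275)/2 = 0.2338. √(0.2494/0.2338) = 1.033, so the standard error is about 3% too wide.

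**F. Birth window.** Gestational age runs from about two weeks before conception. A 40-week birth falls within 52 weeks of enrolment only if conception occurs by week 52 − 38 = 14; a 32-week birth, by week 52 − 30 = 22. Births seen by one year may over-represent preterm ones, and earlier conception in one arm would alter that mix.

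**The case against.** Several points on the other side stand.

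- Chi-square is a valid test for a binary outcome. Its limitation here is only that it takes no account of cohort and centre.
- A reader might infer that the plan will fit ANCOVA to yes/no data. The sentence does not say so; it lists two methods for two outcomes, and ANCOVA may be meant for a continuous measure such as birth weight. No such measure is named, so the wording needs tidying, but a wrong model is not established.
- A reader might also take pooling as settled. It rests on the wording of secondary outcome 3 alone. The Statistical analysis section does not repeat it, and the article elsewhere calls the cohorts independent and sets a recruitment target for each.
- The same wording could mean all participants as denominator, which would keep the randomised comparison. Birth prevalence normally means per birth, and an outcome open to two denominators that can give different answers still needs fixing.
- The 1.7-point excess in illustration A is not a forecast of harm. It rests on an assumed doubling of risk in added births, and the sign reverses at 5%. With 500 and 600 births (1000 women per arm, both cohorts), the standard error is √(0.10×0.90/500 + 0.1167×0.8833/600) = 1.9 points, so the excess is about 0.9 standard errors and would seldom be declared significant.
- Birth without a Big-3 complication follows the birth rate. In illustration A the rise from 45% to 53% comes wholly from added births. It cannot alone answer whether Big-3 risk falls, so it should not displace the Big-3 outcome.

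Adjustment for strata in secondary analyses is a detail that an article may leave to a fuller plan, and by itself it would not be a finding. What does not fall away is that the stated measure conditions on a post-randomisation event that the trial hopes to change.

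**Conclusion.** The point holds for a secondary outcome. On its natural reading, Big-3 is compared among births. That comparison is not protected by randomisation if the programme raises pregnancy as intended, and it can mislead in either direction. The size cannot be fixed from the documents. Under assumed rates it is mostly about 1 to 2 percentage points, nearly 4 in the outer case of illustration C, and zero when added births carry the same risk as the rest. A changed cohort mix under pooling adds 0 to 1.1 points in illustration D. The loss of precision from ignoring strata is minor, about 3%.

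It would be going too far to say that the chi-square is invalid, that the plan certainly pools the cohorts, that it certainly applies ANCOVA to binary data, or that the trial would report harm. The text does not settle the second and third, and the last depends on risks that the documents do not give. The primary dietary risk score analysis and its sample size are untouched.

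**What to change.** 1. State the denominator. Analyse pregnancy, birth with a Big-3 complication and birth without one, each per randomised woman, by logistic or log-binomial regression or by Mantel-Haenszel, adjusted for or stratified by cohort and centre. Give a 95% confidence interval, and show results by cohort.
2. Keep Big-3 among births as a reported secondary estimate, since the Objectives ask about that risk. Adjust it for cohort, count it per woman so that multiple births are not treated as independent, label it as conditional on birth, and read it beside the birth rate.
3. Limit ANCOVA to continuous measures and name them.
4. State the window in which births are ascertained, and how women still pregnant at the one-year questionnaire are handled. Say whether the medical record validation mentioned in the Discussion captures later births.

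Items 1 to 3 cost wording, a little more analysis work and a more cautious reading of the Big-3 result. Item 4 is also wording, unless later births are to be counted and the record validation does not already reach them, in which case some further follow-up is needed.

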#### Tertiary outcomes

The influence of participation of men, pregnancy, age, low socioeconomic status on the primary outcome and 1) Improvement (defined as the percentage of reduction) of unhealthy nutrition and lifestyle 36 weeks after starting the “Smarter Pregnancy” intervention; 2) the compliance and reliability of “Smarter Pregnancy” among both women and men. To study the latter, we aim to determine the: 1) The percentage of the target group that meets all the inclusion criteria for the study, but does not participate; 2) The percentage of participants that is still participating after three months (compliance); 3) The prevalence and nature of technical problems.

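### Pregnancy during participation, which the trial expects the intervention to increase, is planned as an ordinary subgroup variable, so arm comparisons within its strata are not protected by randomisation

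*Protocol article*

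**What the plan says.** The last paragraph of Statistical analysis in the protocol article lists four variables to be studied: "The influence on the primary outcome of participation of men, if pregnancy occurred during participation, age and low socio economic status will be analyzed". One of them is a pregnancy arising after entry: "if pregnancy occurred during participation". All four are handled alike, "by including these variables and their interaction with both groups, one by one in the model which will be used for the primary outcome". The reporting rule is conditional: "If there is heterogeneity of the treatment effect, the effect will be determined per subgroup separately". The Tertiary outcomes section sets the rank of this analysis: "The influence of participation of men, pregnancy, age, low socioeconomic status on the primary outcome".

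Elsewhere the article treats pregnancy as something the intervention should change. The Objectives state that "we will determine whether couples will have a higher pregnancy rate". The Secondary outcomes include "pregnancy rates in couples". The Discussion expects to show the program's effectiveness and "its positive effect on reproductive and pregnancy outcome in both fertile and subfertile couples".

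**The concern.** Age and socio-economic status exist before randomisation, so the arms remain comparable within their levels. Pregnancy during the program does not have that property. If coaching helps some women conceive, the pregnant stratum of the intervention arm contains women whose counterparts in the control arm sit in the non-pregnant stratum. Any trait that favours both conception and a low DRS is then distributed differently between arms inside each stratum.

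A second problem is separate from selection. If becoming pregnant itself changes diet, holding pregnancy fixed removes that route from the estimated effect.

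At stake is the reading of the tertiary result. A reader would naturally take an effect in women who became pregnant as a randomised comparison, and the plan attaches no caveat to it.

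**Working it through.** **1. Is the variable post-randomisation?** Under Eligibility, women enter while contemplating pregnancy. The Control group section and the Fig. 2 caption have pregnancy status updated every 6 weeks. The Primary outcome section mentions people who are already pregnant, but the analysis sentence refers to pregnancy occurring during participation, so reading it as baseline status does not fit the text.

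**2. Is it expected to respond to treatment?** Yes, by the Objectives, the Secondary outcomes and the Discussion. Statistical analysis itself also tests the effect of the intervention on the pregnancy outcome. One section thus uses pregnancy both as an outcome of treatment and as a modifier of treatment.

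**3. The plan's own figure.** The article gives no number for this analysis. Its design inputs, used below, do reproduce: n per arm = 2 × (1.960 + 0.842)² × 2.7² / 0.5² = 457.7, rounded up to 458, or 916 in total, as stated under Statistical considerations.

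**4. Illustration of size.** From the documents: effect -0.5, SD 2.7. Assumed: baseline to 24-week correlation 0.5; about 30% of controls pregnant; an unmeasured trait U ~ N(0,1), such as motivation, that raises the odds of pregnancy and lowers DRS. The pregnancy odds ratio (OR) of 1.65 borrows only its size from the 65% that the Background reports for the earlier outpatient clinic; 2.5 is an upper variant.

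- logit P(pregnant) = -0.85 + ln(OR) × arm + g × U
- DRS at 24 weeks = 0.5 × baseline - 0.5 × arm + b × U + error, with error variance 2.7² × 0.75 - b²
- Moderate shared cause: g = 0.5, b = -0.8. Strong: g = 1.0, b = -1.35.
- Fitted as the article describes: DRS on arm, pregnancy, arm × pregnancy and baseline DRS; 4,000,000 simulated women per scenario.

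| Arm OR on pregnancy | Shared cause | Pregnant, control / intervention | Effect without split | Not pregnant | Pregnant |
|---|---|---|---|---|---|
| 1.00 | strong | 33% / 33% | -0.50 | -0.50 | -0.50 |
| 1.65 | none | 30% / 41% | -0.50 | -0.50 | -0.50 |
| 1.65 | moderate | 31% / 42% | -0.50 | -0.45 | -0.46 |
| 1.65 | strong | 33% / 43% | -0.50 | -0.39 | -0.38 |
| 2.50 | moderate | 31% / 52% | -0.50 | -0.42 | -0.42 |
| 2.50 | strong | 33% / 51% | -0.50 | -0.30 | -0.28 |

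A repeat with another random seed agreed to within about 0.013. The true effect is the same in every woman, so each departure from -0.50 in the last two columns comes from the split alone.

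**5. The route through pregnancy.** Let pregnancy also lower DRS by 0.8 (assumed), with OR 1.65 and a moderate shared cause. The expected total effect is -0.5 - 0.8 × (0.419 - 0.309) = -0.588; simulated, -0.58. Both strata show -0.46. Of the gap of about 0.13, some 0.09 is the dropped route through pregnancy and some 0.04 is selection.

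**6. Precision.** With 450 analysed women per arm (500 less 10%) and a residual SD of 2.33, the OR 1.65, moderate row gives about 139 and 188 pregnant women and 311 and 262 not pregnant. Standard errors are 2.33 × √(1/139 + 1/188) = 0.26 and 2.33 × √(1/311 + 1/262) = 0.20. For the difference between strata, √(0.26² + 0.20²) = 0.33.

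**The case against.** The best defence is that the analysis is tertiary, it asks a fair question about the influence of pregnancy, and the primary intention-to-treat comparison, sample size and secondary outcomes do not depend on it. That is right and it sets the severity. It does not turn the within-stratum contrasts into randomised comparisons.

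The bias is also conditional. It needs an arm effect on pregnancy together with shared causes of pregnancy and DRS. This stands. Still, the trial intends the first, and the second is plausible because the Background and Discussion link nutrition to fertility.

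A reader might infer that the split will create a false interaction and so trigger the per-subgroup rule. The calculations do not show this: the two strata move together and differ by at most about 0.02, against a standard error of about 0.33. What is distorted is the level of both effects.

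A reader might also infer that the effect could come out with the wrong sign. In a simulation with no direct arm effect, pregnancy rising from 31% to 41% and lowering DRS by 1 point, the total effect is about -0.10 and the strata show about +0.04, or +0.07 with a stronger link between trait and conception. But these are different quantities. With no direct effect the within-stratum target is zero, so the selection bias is +0.04 to +0.07. In the scenarios with a true effect of -0.50, the sign never changed.

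Finally, the bias may be small beside the noise. With OR 1.65 and a moderate shared cause, about 0.04 is roughly a fifth of a standard error. With OR 2.5 and a strong one, about 0.20 is close to a full standard error.

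**Conclusion.** The concern holds in a limited form. The article plans a subgroup analysis on a post-randomisation event that it also names as an outcome the intervention should improve, and it treats that event like a baseline characteristic. If the intervention changes pregnancy and pregnancy shares causes with DRS, both stratum effects are biased; any effect that runs through pregnancy is lost as well.

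Under the assumptions shown, a constant -0.50 reads as about -0.46 to -0.28, a loss of 8% to 44%. Pregnancy rates, odds ratios and strength of the shared cause are assumptions, so the range illustrates the mechanism and does not predict this trial's result.

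The documents do not support saying that the subgroup effects are biased whatever happens, that a spurious interaction is likely, or that the main conclusion is at risk. Severity: should-fix.

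**What to change.** Remove pregnancy during participation from the interaction and subgroup list in Statistical analysis and from the matching sentence in Tertiary outcomes, and keep only modifiers whose value is fixed at randomisation.

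If the sponsor wants to retain the question, there are two acceptable forms:

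- a descriptive table of DRS by pregnancy status and arm, with a note that the arms are not comparable by randomisation within it; or
- a mediation or principal-stratum analysis labelled exploratory, with its assumptions stated and no treatment-effect claim per pregnancy subgroup.

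The cost is a text change in two places and the loss of one exploratory subgroup claim. Sample size, data collection and the primary analysis are unchanged.
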